## Hypothesis

The primary hypothesis of this study is that the implemented and standardized laparoscopic surgical technique for right-sided colon cancer will be safe without an increase in the 90 days postoperative morbidity (non-inferiority design).

The second hypothesis is that the quality of surgery, objectively assessed by competency assessment, is an important determinant for long-term clinical patient outcomes.

The clinical outcomes of the surgical technique to treat right-sided colon cancer will be improved by safely implementing a standardized method according to the latest evidence. Improvements in outcome measures that reflect the oncological quality of surgery, such as validated assessment of plane of dissection and vascular ligation, grading of the resection specimen, total lymph node count and number of resected positive lymph nodes and completeness of mesocolic excision based on postoperative CT imaging are expected. Eventually, it is hypothesized that the surrogate oncological endpoints will translate in reduction of local and distant recurrences and improved 5-year overall survival (OS) and 3-year disease free survival (DFS).

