### Secondary study parameters/endpoints

- Intraoperative complications (i.e. vascular injury, injury to other organs);
- 90-day mortality;
- Conversion;
- Operative time;
- Blood loss;
- Validated assessment of plane of dissection;
- Validated assessment of level of vascular ligation;
- Grading of the resection specimen according to Benz et al. [17];
- Total lymph node count;
- Number of resected positive lymph nodes;
- Resection margins;
- Completeness of mesocolic excision based on postoperative CT imaging;
- Locoregional recurrence;
- Distant metastasis;
- 3-year disease free survival (DFS);
- 5-year overall survival (OS);
- Long-term morbidity: incisional hernia, adhesion related small bowel obstruction, readmissions, reinterventions, anastomotic leakage.

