   3. Prospective inclusion of consecutive patients undergoing laparoscopic right hemicolectomy in the participating hospitals in three months.
2. **Delphi phase**: Development of Standard Laparoscopic Right Hemicolectomy: an (inter)national Delphi study
   1. Approaching specialists to participate in the Delphi method (from participating hospitals in step 1).
   2. Identification of crucial steps and measures according to literature and expert’s opinion (Delphi method).
   3. Documentation of steps and the order in which they need to be performed, development of a competency assessment tool (CAT).
3. **Training phase**: Skills center training facility
   1. Training the participating surgeons in the method of the standardized laparoscopic right hemicolectomy, as consented in the Delphi method.
4. **Implementation phase**: implementing the standardized laparoscopic right hemicolectomy with proctoring during another period with prospective inclusion of 365 consecutive patients (total duration of inclusion is 4 months, possibility to extend until maximum of 6 months). N=40+ centers; N=365 videos.
5. **Consolidation phase**: Collection of a third group of 365 consecutive patients with collection of surgical videos in all participating hospitals (total duration of inclusion is 4 months, possibility to extend until maximum of 6 months). N=40+ centers; N=365 videos.
   1. Rating videos.
   2. Comparing with pre-implementation performance based on outcome measures reflecting oncological quality of surgery, and 90-day clinical outcomes.
   3. Comparing with pre-implementation performance based on the long-term outcomes. (3-year DFS and 5-year OS).

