# STATISTICAL ANALYSIS

The clinical outcomes will be categorical or dichotomous outcomes and will be presented as absolute numbers and percentages. The chi-square test will be used for comparing categorical data among patient groups. Descriptive outcomes will be reported as median with interquartile range (IQR) or mean with standard deviation (SD) and in accordance to their distribution the Mann-Whitney-U test is used to evaluate intergroup variation.

Oncological outcome will be determined using Kaplan-Meier analyses, with comparison of relevant patient groups using the log-rank test. Predictors of main outcome parameters will be determined by selecting relevant variables based on expected association with subsequent univariable analysis. Besides stratified comparisons as described above, multivariable analysis will be performed to determine independent association of factors with a specific outcome parameter using logistic and Cox regression analyses. A p-value <0.05 will be considered to be statistically significant. All analyses will be performed with IBM SPSS statistics, version 23.00 (IBM Corp Amonk, NY, United States).

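### The covariate rule in section 10 is not limited to preoperative variables, so a Cox model with phase and nodal findings together would give a biased phase effect on DFS and OS

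*Protocol*

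**What the plan says.** Section 10 gives three statements on the oncological and adjusted analyses.

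- For DFS, OS and recurrence: "Oncological outcome will be determined using Kaplan-Meier analyses, with comparison of relevant patient groups using the log-rank test".
- For variable selection: "Predictors of main outcome parameters will be determined by selecting relevant variables based on expected association with subsequent univariable analysis".
- For the adjusted models: "multivariable analysis will be performed to determine independent association of factors with a specific outcome parameter using logistic and Cox regression analyses".

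No covariate is named, no candidate is excluded, and the timing of candidate variables is not mentioned.

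Section 4.3 lists the measures that the standardized technique is expected to improve, among them "grading of the resection specimen, total lymph node count and number of resected positive lymph nodes". It then says that "it is hypothesized that the surrogate oncological endpoints will translate in reduction of local and distant recurrences", with better 5-year OS and 3-year DFS. Section 8.1.2 has "Number of resected positive lymph nodes", total node count and resection margins as secondary endpoints. The last step of section 8.2 includes "Comparing with pre-implementation performance based on the long-term outcomes", meaning 3-year DFS and 5-year OS. The phases are sequential and not randomised (section 5).

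**The concern.** The only entry criterion for the models is association with the outcome. The protocol itself expects nodal findings to be associated with recurrence, DFS and OS, so they meet that criterion. It also expects the technique to change them, so they are consequences of the intervention and not baseline characteristics. Phase, whose effect on the same outcomes is hypothesised, meets the criterion as well. Followed as written, the rule makes phase and nodal findings candidates for the same Cox model.

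That model answers the wrong question. If a more complete lymphadenectomy finds nodal disease that was previously missed, patients with occult disease move from the node-negative to the node-positive group. The later node-negative group is then purer than the earlier one, and at equal recorded nodal status the later phase looks better although no patient fares better. If the technique works by removing more nodes, holding total node count fixed removes that part of its effect.

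In a before/after study the reader will look to an adjusted phase effect for reassurance about confounding. An adjusted estimate distorted in this way could be read as evidence on long-term oncological benefit, which section 5 names as the ultimate aim.

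**Working it through.** **1. The protocol's own figure.** The sample size is the only design figure that can be recomputed. With 26% morbidity in both groups, a 7-point margin, one-sided alpha 0.05, 80% power and 1:2 allocation, the control group needs (1.645 + 0.842)² × 0.26 × 0.74 × (1 + 1/2) / 0.07² ≈ 364.1, rounded up to 365. The other group is then 730 and the total 1095, as section 6.4 states. The present point does not depend on this calculation; it supplies only the group sizes for step 3.

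**2. Stage migration by hand.** All inputs are assumed, since the protocol gives none. Of 100 patients, 57 are truly node-negative (3-year DFS 88%), 8 have occult positive nodes (78%) and 35 overt positive nodes (68%). The technique has no effect on DFS. The control phase records the 8 as node-negative; the later phase records them as node-positive.

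- Recorded node-negative: control DFS = (57 × 0.88 + 8 × 0.78)/65 = 0.868; later DFS = 0.88. Ratio of −ln(DFS) = 0.1278/0.1419 = 0.90.
- Recorded node-positive: control DFS = 0.68; later DFS = (8 × 0.78 + 35 × 0.68)/43 = 0.699. Ratio = 0.3587/0.3857 = 0.93.
- All patients: DFS = (57 × 0.88 + 8 × 0.78 + 35 × 0.68)/100 = 0.802 in both phases. Ratio = 1.00.

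This is close to a worst case: detection of node-positive patients rises from 35/43 = 81% to 100%.

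**3. Simulated Cox models over a range.** The setting was 365 against 730 patients, follow-up to 3 years, 2000 runs per row and two-sided 0.05. Assumed inputs were 38% truly node-positive, a node-negative hazard of 0.05 per year, a nodal hazard ratio of 2.5 or 4, detection of 75-90% before and 95% after, and no true effect of the technique. Occult and overt disease share one hazard here.

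| Detection before → after | Nodal HR | Phase HR, no nodal term | Phase HR, recorded nodal status in model | P(significant, favours new): no nodal term | P(significant, favours new): nodal term |
|---|---|---|---|---|---|
| 90% → 95% | 2.5 | 1.00 | 0.98 | 0.028 | 0.032 |
| 90% → 95% | 4 | 1.00 | 0.98 | 0.022 | 0.036 |
| 85% → 95% | 2.5 | 1.00 | 0.96 | 0.025 | 0.043 |
| 85% → 95% | 4 | 1.00 | 0.95 | 0.036 | 0.066 |
| 75% → 95% | 2.5 | 1.00 | 0.94 | 0.025 | 0.076 |
| 75% → 95% | 4 | 0.99 | 0.90 | 0.031 | 0.135 |

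Recorded nodal status passed univariable selection in essentially every run.

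Hand check of the third row: the occult share among recorded node-negatives is 0.38 × 0.15/(0.62 + 0.057) = 8.4% before and 0.38 × 0.05/(0.62 + 0.019) = 3.0% after. The initial hazard ratio in that stratum is (1 + 1.5 × 0.030)/(1 + 1.5 × 0.084) = 0.93. In the node-positive stratum it is 1.00. The pooled 0.96 lies between them.

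**4. Total node count works the other way.** Assume mean counts of 20 before and 26 after, and a real benefit running wholly through yield, with hazard ratio 0.7 per 10 nodes. The expected phase effect is about 0.7^0.6 = 0.81. In simulation (detection 85% → 95%, nodal hazard ratio 2.5) the phase hazard ratio was 0.82 without adjustment, 0.79 with nodal status in the model, and 1.00 with total node count in the model. In the last case the benefit disappears.

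**The case against.** The strongest reply is that section 10 describes predictor modelling and not an adjusted phase comparison. It speaks of predictors and of independently associated factors, which fits the aims of relating technical variation and surgical quality to outcome. It does not say that phase is a model term. The stated comparison of oncological outcome is Kaplan-Meier with a log-rank test, and on the arithmetic above an unadjusted comparison is free of this bias. The section refers back to stratified comparisons but names no stratifier, so stratification by nodal status cannot be read into it. Covariate lists are also commonly left to an SAP.

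Much of this stands. A reader might infer that the protocol's DFS and OS comparison is itself biased, or that the rule is bound to produce an apparent oncological gain. The text supports neither: no covariate is named, and the log-rank comparison carries no nodal term. Nor does every postoperative variable push towards the new technique. That direction holds for nodal status, positive nodes and pathological stage; total node count can do the opposite.

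What does not stand is that this is only a missing list. The protocol states a rule, and the rule is outcome-driven. An SAP that followed it would inherit the problem. The models seek factors independently associated with outcome, and by the hypotheses in section 4.3 both the technique and the nodal findings are expected to be such factors. Multivariable regression is also the only adjustment for confounding that section 10 describes for a non-randomised comparison.

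**Conclusion.** The point holds in a limited form. The selection rule admits consequences of the intervention, and any Cox model that includes phase alongside them yields a biased phase effect.

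For nodal status, with no true benefit, the phase hazard ratio falls to 0.90-0.98. The chance of a falsely significant result in favour of the new technique is 0.03-0.14, against 0.02-0.04 without the nodal term. The bias is small when detection improves little and material only when it improves a great deal. For total node count the bias can run against the new technique.

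These sizes rest on assumed nodal prevalence, prognosis and detection rates, none of which the protocol gives. The conclusion that the adjusted effect is biased rests only on the protocol's own expectation that nodal findings will change and will relate to outcome. DFS and OS are secondary endpoints; stage migration does not bear on 90-day morbidity, and the sample size is untouched.

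**What to change.** Add to section 10, and carry into any SAP, text to this effect:

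*Any model used to estimate a difference between phases will adjust only for preoperative variables named in advance (for example age, ASA class, clinical stage and tumour location). These variables will not be chosen by univariable screening. Pathological stage, node counts and resection margins are analysed as outcomes, or enter only prognostic models in which no phase effect is interpreted.*

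The existing selection rule can remain for the purely prognostic models. No new data should be needed: the flowsheet in section 13.1 already has forms for patient characteristics, preoperative CT and preoperative tumour characteristics (CRF 2 to 4). The cost is a few sentences and a slight loss of precision from not conditioning on pathological stage.

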## Other study objectives

- To evaluate current practice and variations in technique for laparoscopic right hemicolectomy in the Netherlands.

- To give an overview of the vascular anatomical variations pertinent to laparoscopic right hemicolectomy.

- To evaluate the association of each variation performed in laparoscopic right hemicolectomy with the short- and long-term clinical and oncological outcomes.

- To reach consensus for a standardized step wise technique for laparoscopic right hemicolectomy using the most recent insights in optimized colon cancer surgery from literature and the results from the assessment during the first phase of the study, according to the Delphi method.

- Development and validation of a Competency Assessment Tool (CAT) for the standardized right hemicolectomy using surgical full-length videos of the laparoscopic right hemicolectomy procedures and the steps as identified in the Delphi method.

- To train and implement the standardized surgical technique in centers in the Netherlands for patients with right-sided colon cancer.

- To evaluate the short- and long-term clinical and oncological outcomes of the cohort after training and compare these with the cohort before training, implementation and proctoring of the standardized technique.

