# STUDY DESIGN

The design of this trial is a multicenter prospective interventional sequential cohort study with a transition period in which implementation of the standardized technique is performed in the same centers after education and hands on training. Proctoring of the new technique will be provided during implementation. The second data evaluation of the clinical and oncological outcomes of the consecutive patient group will be collected in the group of patients after proctoring is finished, the so called consolidation phase. This study is primarily designed as a non-inferiority trial, based on short-term postoperative complications, with the aim of ultimate improvement of long-term oncological outcome. The accrual of both the control patients and the patients after implementation will be within the national Prospective Dutch ColoRectal Cancer cohort (PLCRC) with additional video analysis and image collection with additional informed consent. The primary endpoint is safety during implementation of a new technique. This is measured by 90-day morbidity with the Clavien-Dindo classification [15]. The assumption is that the perioperative morbidity (26% 30-day overall postoperative complication rate; as earlier published based on the DCRA database [16]) will not be increased by implementation of the new standardized technique with a non-inferiority margin of 7%, therefore not exceeding 33%.

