## Sample size calculation

Sample size calculation is performed with the aim to demonstrate safety with non-inferiority for the primary endpoint overall 90-day morbidity. If there is truly no difference between the standard and experimental treatment, then 1095 patients (365 patient in each of the three groups) are required to be 80% sure that the lower limit of a one-sided 95% confidence interval (or equivalently a 90% two-sided confidence interval) will be above the non-inferiority limit of 7%. Therefore, in the one group 365 patients will be included (control group) and in the other group 730 patients will be included (implementation and consolidation phase together).

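### Section 10 makes a univariable step part of choosing predictors, which fits poorly with the aim of evaluating each technique variation and tends to inflate modest associations in the 365-patient cohort

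*Protocol*

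**What the plan says.** Section 10 (Statistical analysis) sets out how predictors are found: "Predictors of main outcome parameters will be determined by selecting relevant variables based on expected association with subsequent univariable analysis". It then says that "multivariable analysis will be performed to determine independent association of factors with a specific outcome parameter using logistic and Cox regression analyses". The only p-value in the section is the general one: "A p-value <0.05 will be considered to be statistically significant". Section 10 gives no cut-off for entering the multivariable model, no rule that factors failing the univariable step are excluded, and no rule on whether their estimates are reported.

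Section 4.2 (Other study objectives) includes the aim "To evaluate the association of each variation performed in laparoscopic right hemicolectomy with the short- and long-term clinical and oncological outcomes". The technique elements listed in Section 8.2 (Study procedures) are approach, number and positioning of trocars, dissection plane, level of vascular ligation, anastomotic technique and extraction site. Current practice is mapped in the control cohort of 365 patients.

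**The concern.** Candidates are first chosen on expected association, which is a sound subject-matter step. A univariable look at the outcome data then forms part of how predictors are settled. If that look acts as a filter, three things follow.

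- A technique variation that fails it gets no adjusted estimate, although the objective covers every variation.
- A confounder can fail it and be left out of the adjustment, which can bias the remaining estimates in either direction.
- A factor with a modest effect passes mainly when chance has pushed its estimate up, so the retained estimate is too large on average. Its confidence interval takes no account of the selection.

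At stake are the adjusted technique-outcome associations, above all those from the 365-patient control cohort, where precision is lowest.

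**Working it through.** **The plan's own figure.** Section 5 (Study design) gives a "26% 30-day overall postoperative complication rate" and a margin of 7 percentage points. Section 6.4 gives 80% power, one-sided 5%, and 365 against 730 patients.

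n(control) = (1.645 + 0.842)² × 0.26 × 0.74 × (1 + 1/2) / 0.07² ≈ 364.1, rounded up to 365, with 730 in the other group and 1095 in total. The stated sample size is reproduced. It involves no predictor model, so this point does not affect it.

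**Events available.** 0.26 × 365 = 94.9, about 95 in the control cohort. 0.26 × 1095 = 284.7, about 285 overall. These apply the 30-day rate to 90-day morbidity, as the protocol does.

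**Assumptions the protocol does not supply.** One binary technique factor used in 50% (or 20%) of operations, true odds ratio (OR) 1.3 to 2.0, filter at p<0.05 (0.20 also shown).

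**Analytic check, 50% prevalence, p<0.05.** With β = log OR:

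- SE ≈ √[4 / (n × 0.26 × 0.74)], which is 0.239 at n=365 and 0.138 at n=1095.
- Probability of passing ≈ 1 − Φ(c), where c = 1.96 − β/SE.
- Mean log OR among those passing ≈ β + SE × φ(c) / [1 − Φ(c)].

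n=365, OR 1.3: β = 0.262, c = 0.861, passing 0.195. Mean log OR = 0.262 + 0.239 × 1.415 = 0.600, so OR 1.82.

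n=365, OR 1.5: β = 0.405, c = 0.261, passing 0.397. Mean log OR = 0.405 + 0.239 × 0.971 = 0.637, so OR 1.89.

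n=1095, OR 1.5: c = −0.983, passing 0.837. Mean log OR = 0.405 + 0.138 × 0.294 = 0.446, so OR 1.56.

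**Simulation, 40,000 replicates per setting.** Mean OR is the exponential of the mean log OR.

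| n | Prevalence | True OR | Mean, no filter | Pass at p<0.05 | Mean if passed, p<0.05 | Mean if passed, p<0.20 |
|---|---|---|---|---|---|---|
| 365 | 50% | 1.3 | 1.30 | 19% | 1.83 | 1.60 |
| 365 | 50% | 1.5 | 1.50 | 39% | 1.90 | 1.71 |
| 365 | 50% | 2.0 | 2.00 | 81% | 2.17 | 2.06 |
| 365 | 20% | 1.3 | 1.30 | 16% | 1.98 | 1.68 |
| 365 | 20% | 1.5 | 1.50 | 31% | 2.06 | 1.81 |
| 1095 | 50% | 1.3 | 1.30 | 47% | 1.46 | 1.38 |
| 1095 | 50% | 1.5 | 1.50 | 83% | 1.56 | 1.52 |
| 1095 | 50% | 2.0 | 2.00 | 100% | 2.00 | 2.00 |

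**Screen followed by a multivariable model.** A separate simulation (1500 replicates) used seven technique items, each at 50% prevalence with true OR 1.4 and a filter at p<0.05. At n=365 an item survived 27% of the time with a mean OR of 1.87 and 95% interval coverage of 91%. Without the filter these were 1.41 and 95%. At n=1095, 66% survived, with a mean OR of 1.51 against 1.40 unfiltered.

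The three calculations agree. Distortion is marked for modest effects at n=365, small for an OR of 1.5 at n=1095, and absent for an OR of 2.0 at n=1095. A more lenient filter reduces it but does not remove it.

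**The case against.** The best reply is that Section 10 does not spell out a filter. It gives no entry threshold, does not limit the multivariable model to factors that passed, and does not say that other results go unreported. Such details may sit in a statistical analysis plan that is not at hand. This stands against one tempting inference, that only factors clearing p<0.05 will be reported: the 0.05 is the general significance level, and the reporting consequence is not written down. It does not remove the point, because the univariable step is stated as part of how predictors are determined. A later plan would be implementing that step.

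A reader might also infer that inflated odds ratios will shape the Delphi standard, since Section 4.2 names "the results from the assessment during the first phase of the study" as an input. The documents do not go that far. Those results need not be regression estimates, Section 8.2 has the crucial steps identified from literature and expert opinion, and the Delphi round follows 4 to 6 months of video collection, so disease-free and overall survival cannot inform it.

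A third objection concerns the remedy. About 95 events support only some 7 terms (95/7 ≈ 14 events per term), which the technique elements alone could use up before any confounder enters. Rates for mortality and recurrence are not given, so one full model for every outcome could be overfitted. This stands, and the fix has to allow for it.

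Finally, exaggeration is not general: it fades with strong effects or the full cohort, and omitted confounders can bias either way.

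**Conclusion.** The point holds in a limited form. The protocol fixes a data-driven univariable step for choosing predictors, and that step does not serve an objective covering every technique variation. Under the assumed 50% prevalence and a p<0.05 filter, a true odds ratio of 1.3 to 1.5 in the control cohort would usually be dropped, and would average about 1.83 to 1.90 when kept. In the full 1095 the effect on an odds ratio of 1.5 or more is slight or nil. These sizes rest on assumed prevalences, effects and thresholds; the direction for modest effects at n=365 was the same at every prevalence and threshold tried.

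A reader might take this as a threat to the main result. It is not one: the sentence concerns predictor analyses under the other objectives and does not govern the non-inferiority comparison. The change should be made, but it is not critical to the trial's primary conclusion.

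**What to change.** In Section 10, replace the univariable selection step with wording to this effect: for each outcome, technique factors and confounders are chosen beforehand on subject-matter grounds, in a number suited to the expected events (about 95 morbidity events in the control cohort, about 285 overall). The chosen set stays in the model whatever the univariable p-values, and all estimates are reported with confidence intervals. Univariable results are descriptive only. For outcomes with few events, use a smaller pre-chosen set or penalised regression instead of a screen.

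If no filter was ever intended, the same wording removes the ambiguity. The cost is a few sentences and somewhat wider intervals for single coefficients. No patients are added, and the sample size stays at 1095.

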# TREATMENT OF SUBJECTS

## Investigational treatment

The implementation of the standardized laparoscopic right hemicolectomy with proctoring with prospective inclusion of consecutive patients with collection of surgical videos in all participating hospitals will be investigated. This method will be compared with the laparoscopic right hemicolectomy performed by the same hospitals before the training and implementation of the standardized technique. The clinical outcomes will be collected using the DCRA database and the oncological outcomes will be collected by the surgeons, surgical registrars and/or trained research nurses in the participating centers.

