# METHODS

## Study parameters/endpoints

### Main study parameter/endpoint

The primary endpoint is the 90-day morbidity with Clavien-Dindo classification.

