# APPENDIX

## Study flowsheet showing patient pathway and CRF completion times

Patient pathway: Suggested CRF completion times:

Decision to operate

CRF 1: Registration form

CRF 2: Patient characteristics

CRF 3: Preoperative CT-imaging

CRF 4: Preoperative tumor characteristics

CRF 5: Video and surgical details

CRF 6: Specimen

CRF 7: Pathology

CRF 8: Follow-up 3 months

CRF 9: Follow-up 12 months

CRF 10: 1 year postoperative CT-imaging

CRF 11: Follow-up 36 months

CRF 12: Follow-up 60 months

CRF 7-12

CRF 4-6

CRF 1-3

Patient discharged

Operation

Pre-operative assessment clinic

Routine outpatient review

(around 4-6 weeks)

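### The before-after comparison of non-randomised cohorts is planned with unadjusted tests only, so a modest shift in case mix or centre mix could distort the 7-point non-inferiority conclusion

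*Protocol*

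**What the plan says.** Protocol section 5 describes a "multicenter prospective interventional sequential cohort study with a transition period in which implementation of the standardized technique is performed in the same centers". Section 7.1 fixes the comparator: "This method will be compared with the laparoscopic right hemicolectomy performed by the same hospitals before the training and implementation of the standardized technique". There is no randomisation, so the contrast is between earlier and later patients. Section 8.1.1 sets the endpoint: "The primary endpoint is the 90-day morbidity with Clavien-Dindo classification".

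Section 10 assigns the chi-square test to categorical outcomes, Mann-Whitney U to continuous ones and the log-rank test to oncological outcomes. None of these uses covariates. Logistic and Cox regression follow under a different aim, finding predictors, with candidates chosen by "selecting relevant variables based on expected association with subsequent univariable analysis". The next sentence reads: "Besides stratified comparisons as described above, multivariable analysis will be performed to determine independent association of factors with a specific outcome parameter". Nothing before it in section 10 describes a stratified comparison.

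Section 6.4 sizes the trial for a crude difference of two proportions, 365 control patients against 730 from the implementation and consolidation phases together.

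**The concern.** Without randomisation, the crude difference between cohorts combines the effect of the technique with any systematic difference in who was operated on, and where. Section 8.2 sets only a total for each phase, 365 patients over 40 or more centres (365/40 is about 9 per centre), with no quota by centre. Patients enter by individual consent before surgery, so the consenting group can also change between phases.

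The direction matters. If the later patients are at lower risk for reasons unrelated to the technique, the crude difference moves towards non-inferiority, and a harmful change could be declared safe. If they are at higher risk, a safe technique could fail. As written, section 10 offers no planned estimate that separates these explanations for the primary endpoint. It offers none for the log-rank comparisons of disease-free and overall survival either.

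**Working it through.** **Inputs from the protocol.** Control rate 26% and margin 7 points (section 5); true difference 0, one-sided 5%, power 80%, 365 against 730 (section 6.4). The 26% is a "26% 30-day overall postoperative complication rate" used for a 90-day endpoint; it is taken as given here. The decision rule used below is the one in section 6.4: a two-sided 90% confidence interval read against the margin.

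**Reproducing the stated size.** With 1:2 allocation and unpooled variance,

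n(control) = (1.645 + 0.842)² × [0.26×0.74 + 0.26×0.74/2] / 0.07² = 6.183 × 0.2886 / 0.0049 = 364.1, rounded up to 365.

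This gives 365 + 730 = 1095, as stated. The standard error with no difference is √(0.1924/365 + 0.1924/730) = 0.0281, and power is Φ(0.07/0.0281 − 1.645) = 80.1%.

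**Effect of a shift.** Let b be the change in expected morbidity of the later cohorts that comes only from patient or centre mix. The probability of declaring non-inferiority is

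Φ((0.07 − d)/SE − 1.645), where d = true difference + b.

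The protocol gives no value for b, so a range is assumed.

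| Size of shift | False non-inferiority (true difference +7 points, shift favourable) | Power (true difference 0, shift unfavourable) |
|---|---|---|
| 0 points | 5.0% | 80.1% |
| 1 point | 9.7% | 68.5% |
| 2 points | 17.2% | 54.8% |
| 3 points | 27.6% | 40.6% |

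Worked cell: with a favourable shift of 2 points the later rate is 31%. SE = √(0.1924/365 + 0.2139/730) = 0.0286, and Φ(0.02/0.0286 − 1.645) = 17.2%.

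If only one later phase were compared with control (365 against 365), the false non-inferiority rate would be 8.9% at 1 point and 14.8% at 2 points. Power would be 57.6% and 45.1%, from a starting value of 69.5%.

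**What could produce such a shift (assumed examples).**

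- Case mix: take a risk factor with odds ratio 2, present in 30% of controls, with overall risk 26%. Risk is then 21.8% without the factor and 35.8% with it. If prevalence falls to 20%, expected morbidity changes by −0.10 × (35.8 − 21.8) = −1.4 points. For odds ratios of 1.5 to 2.5 the change is −0.8 to −1.9 points. At 1.4 points the false non-inferiority rate is about 12%; the opposite shift gives power of about 63%.
- Centre mix: suppose two groups of centres have 20% and 32% morbidity and each supplies half the control cohort. If the lower-risk group's share rises to 60%, expected morbidity is 0.6×20 + 0.4×32 = 24.8%, a shift of −1.2 points. At 70% it is 23.6%, a shift of −2.4 points.

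**The case against.** The design does contain safeguards. The cohorts come from the same centres and inclusion is meant to be consecutive. One set of eligibility criteria removes several strong risk drivers, including ASA 4, cT4b, M1, emergency surgery, obstruction and perforation. Each inclusion window is 4 to 6 months. A reader might infer that nothing keeps the cohorts comparable; that goes too far. These features make large shifts less likely. They do not fix each centre's share or each cohort's risk profile.

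Section 10 does plan multivariable regression, and its wording does not forbid entering cohort as one of the factors. A reader might infer that adjustment of the cohort effect is excluded; the text does not say so. The exact covariate list could properly be left to a statistical analysis plan. What stands is that the protocol itself states a method for comparing groups, that the method is unadjusted, and that the regression is given another purpose.

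The case-mix example needs a systematic change. A fall from 30% to 20% is about 3.4 standard errors at these sizes (SE = √(0.21/365 + 0.21/730) = 2.94 points), so it is not ordinary chance imbalance, which the confidence interval already covers. That is why a range of shifts is shown.

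A reader might also infer that univariable selection by itself badly inflates error. The protocol states no entry threshold, so this cannot be derived from it. A simulation was run with 365 and 730 patients and four binary confounders (prevalence 30%, odds ratios 1.3 to 2.0, shifts of 0 to 10 points in each). With entry at p<0.05 it gave 3.9–6.9% false positives, against 3.6–5.9% with all four kept. The unadjusted test gave 12–48% at the 10-point shift. The weight of the point therefore lies on the crude comparison.

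**Conclusion.** The point holds. For a non-randomised before-after safety comparison, section 10 specifies unadjusted tests, does not name cohort as an exposure in any model, and refers to stratified comparisons that it does not describe. Shifts of 1 to 2 points in expected morbidity are small beside the 7-point margin. They would still take the false non-inferiority rate from 5% to about 10–17%, or power from 80% to about 69–55%.

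These figures rest on the 26% control rate, the 365:730 comparison, the confidence-interval rule of section 6.4 and assumed shift sizes. The protocol gives no evidence that a shift will occur or in which direction, so they show sensitivity and are not a forecast of bias. This should be changed, but it does not invalidate the design.

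**What to change.** In Protocol section 10:

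- Define the primary estimate as an adjusted risk difference in 90-day morbidity from a logistic model standardised to the risk-difference scale. Use cohort as the exposure, case-mix covariates fixed in advance, and centre as a random effect or stratum. Read its two-sided 90% confidence interval against 7 points.
- Keep the crude difference as a supportive analysis.
- Use the same fixed covariates in Cox models that compare cohorts on disease-free and overall survival.
- Do not choose confounders for the cohort effect by univariable screening. It may remain for exploratory predictor work.
- Describe the stratified comparisons or delete the reference to them.
- State unmeasured time trend as a limitation, since adjustment does not remove it.

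The natural sources of covariates are the baseline forms in section 13.1 ("CRF 2: Patient characteristics" and CRFs 3 and 4). Only form titles are given there, so the fields they hold must be checked before the list is fixed; it should not be assumed that every wanted covariate is already collected. If they are, the cost is a wording change and modest analyst time. The price is that the primary result then depends on a pre-specified model.
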